### Follow period and study outcome determination

Study participants will be re-evaluated at 6, 12, 18 and 24 months. Only clinical assessments will be performed at 6, 12 and 18 months. At 24 months, however, participants will again be hospitalised for one week for inpatient observation and testing, during which all the pre-randomisation procedures and tests will be repeated to determine study outcomes.

### Unscheduled visit (passive follow-up)

Parents will be instructed to bring the participants to the study clinic for any suspected illness. The ‘chief complaint’ and ‘diagnoses’ will be recorded using a standard list based on the International Classification of Disease (ICD-10) for children. Consent will be sought from parents or guardians of participants who die for a formal post mortem or verbal autopsy if the post-mortem is not possible.

### Concomitant drugs

All concomitant medications taken during the study will be recorded with the indication, dose information, and dates of administration. However, concomitant use of any other tetracycline is prohibited during the 24-month study period. If needed, a macrolide antibiotic will be used. Randomised participants who take prohibited medications will cease participation. Such participants will remain in the trial and will be included in the primary, intention-to-treat analysis, but excluded from the per-protocol analysis. Doxycycline interacts with barbiturates (e.g. phenobarbitone), carbamazepine, cimetidine, hydantoins (e.g. phenytoin), and rifampicin. These drugs decrease the effectiveness of doxycycline and so will not be co-administered. Those requiring rifampicin will cease participation. On the other hand, side effects of other drugs such as digoxin, insulin, methotrexate, warfarin, or theophylline may be accentuated. Patients requiring these medications will be excluded. Doxycycline may also decrease the effectiveness of penicillin. Thus, during the six-week study drug administration period, alternative antibiotics (co-trimoxazole and cephalosporins) will be used if indicated.

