### Assessment of efficacy and safety

#### Primary efficacy outcome

The objective of the trial is to determine if targeting *O.volvulus* through drugs which kill *Wolbachia* can modify the pathogenic processes in nodding syndrome. We will therefore investigate the effects of doxycycline compared to placebo on the presence and titres of serum antibodies to HNPs (identified in the concurrent case-control study) or leiomodin and on inflammatory markers, the microfilaria density and *Wolbachia* load. The primary efficacy measure will be the proportion patients testing positive for and levels or titres of antibodies to HNPs or leiomodin at 24 months.

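### The rule for randomised participants who take prohibited drugs contradicts itself on retention, and the rifampicin rule repeats the withdrawal wording with no retention clause

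*Protocol article*

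**What the plan says.** All the rules at issue stand in one paragraph of the protocol article, under Concomitant drugs.

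- **Prohibited drugs in general:** "Randomised participants who take prohibited medications will cease participation. Such participants will remain in the trial". The second sentence then states that they "will be included in the primary, intention-to-treat analysis, but excluded from the per-protocol analysis".
- **Period of the tetracycline ban:** "concomitant use of any other tetracycline is prohibited during the 24-month study period".
- **Enzyme-inducing drugs, including rifampicin:** "These drugs decrease the effectiveness of doxycycline and so will not be co-administered. Those requiring rifampicin will cease participation". Nothing on follow-up or analysis set is attached to this sentence.

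Three other sections determine what follows from these rules. Under Primary efficacy outcome, the endpoint is the proportion positive for, and the "levels or titres of antibodies to HNPs or leiomodin at 24 months". Under Follow period and study outcome determination, "Only clinical assessments will be performed at 6, 12 and 18 months", and at the 24-month admission "all the pre-randomisation procedures and tests will be repeated to determine study outcomes". Under Statistical analysis, the analysis is by intention to treat, with no exception for any drug.

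**The concern.** A participant cannot both leave a trial and stay in it. The article nowhere defines what ending participation means, and it does not separate stopping study drug from stopping follow-up. Staff who face a participant given a tetracycline at month 10, or one who needs rifampicin, have wording in front of them that supports ending follow-up.

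What is at stake is the primary outcome. Post-baseline antibody testing is scheduled once, at month 24. A participant released earlier has no scheduled post-baseline sample to fall back on and also misses the 24-month secondary measures. The intention-to-treat sentence would still count that person, but with nothing observed on the primary outcome. The missing value would come from the wording of the rule and not from the participant's own decision.

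**Working it through.** The point concerns wording and disputes no figure. The sample size is reproduced only to set the scale.

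**1. The plan's own figure.** Inputs from Sample size: 50% versus 30% positive, 80% power, 5% significance (taken as two-sided), 10% losses. Allocation is 1:1 (Randomisation section).

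- Uncorrected: n = [1.960 × √(2 × 0.40 × 0.60) + 0.842 × √(0.50 × 0.50 + 0.30 × 0.70)]² / 0.20² = 93 per arm.
- With continuity correction: (n/4) × [1 + √(1 + 4/(n × 0.20))]² = 103 per arm.
- Allowing for losses: 103/0.90 = 114.4, rounded up to 115 per arm, 230 in total. The stated 230 is reproduced.

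**2. The two adjacent sentences.** The subject of the second sentence can only be the people named in the first. The first ends their participation; the second keeps them in the trial and in the primary analysis. Taken literally, the two conflict.

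**3. Can the first sentence mean stopping study drug?** Study drug is taken for six weeks (Study design). The tetracycline ban runs for 24 months. During dosing, that reading reconciles the two sentences. After week 6, which is most of the ban, there is no study drug left to stop. The first sentence then either means leaving follow-up, which the second sentence forbids, or has no effect.

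**4. The rifampicin sentence.** It repeats the withdrawal wording. The retention sentence comes earlier in the paragraph and refers to those who take prohibited medications. The text does not say whether rifampicin users fall under it. Followed as written, the rifampicin sentence removes randomised participants.

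**5. Consequence per person.** Scheduled antibody samples are at baseline and month 24 only. Removal at any time between them means no primary outcome. One such participant is 1/230 = 0.43% of those randomised.

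**6. Scale of the total.** The article gives no frequency of tetracycline or rifampicin use, so no total can be derived. As context only, power for 50% versus 30% with 115 randomised per arm (uncorrected normal approximation) is 84.1% at 10% loss and 81.9% at 15%. The 15% is an assumption. On that calculation, a handful of extra losses would not take power below 80%.

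**The case against.** The strongest reply is that the paragraph largely corrects itself. The second sentence is the more specific, follows at once, and agrees with the intention-to-treat statement under Statistical analysis. An error needs someone to act on one sentence and ignore the next. This stands as far as intent goes: for prohibited drugs, the retention rule is given. It does not remove the contradictory sentence, and it does not clearly reach the rifampicin sentence.

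A second reply is that this article condenses a fuller protocol, where withdrawal procedures and drug windows would normally be set out. That disposes of one complaint: the lack of a stated period for the rifampicin rule is detail the full document may supply, and it is not counted here. The reply does not cover an instruction that is printed and conflicts with its neighbour.

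A reader might also infer more than the text supports:

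- **That different sites will apply the rule differently.** The trial is based in one hospital, with standard procedures and training (Data management) and internal and external monitoring (Study monitoring and data quality control). The remaining risk is how the staff there apply the rule.
- **That these participants are dropped from the primary analysis.** The text says the opposite for prohibited drugs, and it does not say so for rifampicin. The risk is a missing outcome, not a changed analysis set.
- **That the result would be biased or the trial underpowered.** No rate, arm imbalance or direction is given from which either could be argued.

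**Conclusion.** The contradiction is real and is in operative text. Retention is the evident intent, but the first sentence denies it, and the rifampicin sentence repeats the denial without a correction. Followed literally, either sentence would create avoidable missing primary outcomes, because the only scheduled post-baseline antibody test is at month 24.

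The effect is unknown in total and probably small. The conclusion rests on two readings: that ending participation carries its ordinary meaning, since the article gives no other, and that no antibody samples are taken between baseline and month 24, as the visit schedule states. It should be corrected because the correction is simple and a 24-month outcome that was never collected cannot be recovered. It does not call the design, the sample size or the planned analysis into question.

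**What to change.** In Concomitant drugs, replace the withdrawal wording in both the prohibited-drug sentence and the rifampicin sentence with: *will discontinue study drug if still being taken and will continue all follow-up, including the 24-month assessment, unless consent is withdrawn; they are included in the intention-to-treat analysis and excluded from the per-protocol analysis only*.

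The condition on study drug still being taken makes the same sentence work both during and after the six weeks of dosing. The cost is two wording changes in one paragraph and at most a few more 24-month assessments, which the existing intention-to-treat sentence already implies.

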### Data collection and management

#### Data collection

Data will majorly be quantitative and will be obtained from clinical observations, interviews, patient maintained logs, neurophysiologic and cognitive testing, brain imaging and testing of tissue samples. Data will be collected and recorded at the point of contact at the health facility or the participants’ home. Cognitive function on the CogState is exclusively electronic and no additional entry required. Follow up data obtained during home visits will also be collected electronically but all the other data will be paper based. Data forms will be checked at the end of each day for completeness and accuracy.

#### Data management

Prior to the start of the study, we will develop standard operating procedures for all documentation. Study personnel will undergo training in procedures and documentation. Updates of this training will again be provided in the second and third years. Paper based data will be double entered into the databases with validation limits. Once data entry and cleaning are completed, any hard copies of case record forms will be stored for a minimum 7 years as per local guidelines.

### Study monitoring and data quality control

Internal monitoring of the study will be performed by Makerere University Clinical Trials Unit in collaboration with the Amsterdam Institute for Global Health and external monitoring by the East African Consortium for Clinical Research Monitors. In each case, at least five quality audits are provided for.

### Assessment of efficacy and safety

#### Primary efficacy outcome

The objective of the trial is to determine if targeting *O.volvulus* through drugs which kill *Wolbachia* can modify the pathogenic processes in nodding syndrome. We will therefore investigate the effects of doxycycline compared to placebo on the presence and titres of serum antibodies to HNPs (identified in the concurrent case-control study) or leiomodin and on inflammatory markers, the microfilaria density and *Wolbachia* load. The primary efficacy measure will be the proportion patients testing positive for and levels or titres of antibodies to HNPs or leiomodin at 24 months.

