**Methods:**

This will be a two-arm, double-blind, placebo-controlled, randomised phase II trial of doxycycline 100 mg daily for six weeks in 230 participants. Participants will be patients’ ages≥8 years with nodding syndrome. They will receive standard of care supportive treatment. All will be hospitalised for 1–2 weeks during which time baseline measurements including clinical assessments, EEG, cognitive and laboratory testing will be performed and antiepileptic drug doses rationalised. Participants will then be randomised to either oral doxycycline (Azudox®, Kampala Pharmaceutical Industries) 100 mg daily or placebo. Treatment will be initiated in hospital and continued at home. Participants will be visited at home at 2, 4 and 6 weeks for adherence monitoring. Study outcomes will be assessed at 6, 12, 18 and 24-month visits. Analysis will be by intention to treat. The primary efficacy outcome measure will be the proportion of patients testing positive and the levels or titires of antibodies to host neuron proteins (HNPs) and/or leiomodin at 24 months. Secondary outcome measures will include effect of the intervention on seizure control, inflammatory markers, cognitive function, disease severity and quality of life.

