We hypothesise that, nodding syndrome is a neuro-inflammatory disorder, caused by antibodies to antigens from either *O.volvulus* or its symbiont, *Wolbachia*, cross reacting with host neuron proteins (HNPs). Antibodies against HNPs such as the voltage-gated potassium channel complex (VGKC-complex) including the leucine-rich glioma inactivated − 1(LGI1) protein and contactin-associated protein-like-2 (CASPR2), the N-methyl-D-aspartate (NMDA), α-amino-3-hydroxy-5-methyl-4-isoxazolepropionic acid (AMPA), gamma amino-butyric acid (GABA)_A,_ GABA_B_ and glycine receptors are recognised in severe epileptic disorders [20]. Preceding infections may play a role, possibly through molecular mimicry or indirectly by inducing cytokines and allowing pathogenic antibodies gain access to the brain (reviewed in [20, 21]). Two pilot studies have specifically demonstrated evidence of possible cross-reacting antibodies in the pathology of nodding syndrome, including to leiomodin and DJ-1 [2, 22].

*O.volvulus* is transmitted by female blackflies of the genus *Simulium.* Infective larvae are injected into the host during a blood meal. These grow reaching maturity 1–3 years later. The adult worms reside in skin nodules where they can live for 10–15 years producing millions of microfilariae. These migrate under the skin and may be ingested by the next fly to continue the cycle [3]. Ivermectin kills the microfilaria but the adult worm has no specific drug treatment. However, antibiotic depletion of *Wolbachia,* the *O.voluvulus* symbiotic bacteria, with tetracyclines such as doxycycline, results in sterilisation and premature death of the adult worm and marked reduction in dermal microfilaria [23]. The outcome of nodding syndrome could potentially be improved with such a therapy that kills adult *O.volvulus*.

This study aims to examine the effects of treating patients with nodding syndrome, aged 8 years or older, with oral doses of doxycycline 100 mg daily for six weeks compared to placebo, on serum levels of antibodies to HNPs (VGKC complex, leiomodin, DJ-1 and others to be identified in a concurrent case-control study) at 24 months and on seizure control, disease severity, quality of life, ongoing inflammation and microfilaria density. It will also assess safety, adherence to treatment and factors associated with non-adherence.

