### Sample size

From our pilot studies, ~ 50% of patients with prevalent nodding syndrome had antibodies to a HNPs and ~ 60% to leiomodin [2, 22]. We hypothesise that among patients with new onset nodding syndrome (symptoms < 12 months), six weeks’ therapy with doxycycline will cause a 50% reduction in the proportion of patients with and the levels or titres of antibodies to HNPs (a reduction from 50 to 25% compared to placebo) at 24 months. In Uganda, however, there has been no incident cases of nodding syndrome since 2014. It is anticipated that the intervention may not be as efficacious in patients with established symptoms (i.e. patients with symptoms ≥12 months) and the effect on antibodies would be smaller (an anticipated 40% reduction from 50 to 30%). To demonstrate this effect at 80% power and 5% level of significance and allowing for 10% losses to follow up, we will need to recruit a total of 230 patients with established symptoms (115 in either arm).

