#### Secondary efficacy outcomes

Key secondary efficacy measures at 24 months will include:Mean change in serum levels or titres of antibodies to HNPs or leiomodin and serum levels or titres of inflammatory markers.Mean change in dermal microfilaria density on real time PCR at 24 months.The proportions of patients achieving seizure freedom (≥1 month without head nodding or convulsive seizures), mean change in Cogstate scores, the proportions of patients with inter ictal epileptiform discharges on diagnostic EEG, proportion of participants with Gross Motor Function Classification System (GMFCS) scores 3–5; and the proportion of participants with mental health disorders on the MINI-KID and intellectual disability on the CAIDS-Q and the proportion of participants with improved Quality of Life.Others will be mean changes in weight-for-age, height-for-age (stunting), and height-for-weight (wasting) Z-scores and proportions of participants with wasting and stunting (Z-scores <− 3 SD)Incidence rate of non-nodding syndrome sick clinic visits and all cause sick clinic visits; incidence rate of all-cause hospital admissions and all-cause mortality

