### Statistical analysis

Analysis will be by intention to treat. The analysis will compare the proportions of patients testing positive for and the levels or titres of antibodies to HNPs or leiomodin at baseline and at 24 months in both arms. Both crude (unadjusted) and adjusted effect estimates will be computed. The chi square test will be used to compare proportions of children with the different antibodies in the two arms; the Students t-test will be used for means of normally distributed data and the Mann-Whitney U test for skewed data. We will also determine the mean change or reduction in the levels or titres of the antibodies and inflammatory markers with the intervention. Time to event (e.g. to seizure resolution) will be measured from the date of randomisation using Kaplan Meyer Survival analysis and by Cox regression analysis. For the cognitive tests, in addition to classification as impaired or not (in comparison to norms determined from unaffected sibling controls in the concurrent case control study), we will also measure mean improvements in scores. The rates determined will be adjusted for age, HIV infection, weight for height z scores and corrected for multiple testing. We will examine safety (serious adverse events and adverse events) and assess compliance and the factors for poor compliance.

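### The primary outcome bundles at least four antibody comparisons with no success rule, while the 230 patients and the 80% power were worked out for only one of them (HNP positivity)

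*Protocol article*

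**What the plan says.** All references are to the protocol article.

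- **Primary efficacy outcome:** the measure is "the proportion patients testing positive for and levels or titres of antibodies to HNPs or leiomodin at 24 months".
- **Abstract, Methods:** the same outcome, but the two targets are joined differently: "antibodies to host neuron proteins (HNPs) and/or leiomodin at 24 months".
- **Sample size:** pilot positivity is given as about 50% for HNPs and about 60% for leiomodin. The hypothesis mentions levels, but only one contrast has figures: HNP positivity falling from 50% to 30% in patients with established symptoms. The number is set "To demonstrate this effect at 80% power and 5% level of significance" with 10% loss to follow-up, giving 230 (115 per arm). The leiomodin rate is not used, and no mean difference or standard deviation is given for titres.
- **Statistical analysis:** chi-square tests will "compare proportions of children with the different antibodies in the two arms", and levels are compared by t-test or Mann-Whitney test. No comparison is singled out as primary. Later the section says that rates will be adjusted for age, HIV infection, "weight for height z scores and corrected for multiple testing", without naming a family of tests or a method.
- **Background:** the aim refers to "serum levels of antibodies to HNPs (VGKC complex, leiomodin, DJ-1 and others to be identified in a concurrent case-control study", which places leiomodin and DJ-1 inside the HNP group. The abstract and the sections on sample size, primary outcome, secondary outcomes and statistical analysis all set leiomodin beside the HNPs.

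**The concern.** A power statement belongs to one hypothesis, one test and one significance level. Here the primary outcome can be read in several ways, and each reading has its own error rate and power. Two things are at stake.

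First, without a success rule, a significant result on any one of the comparisons could be presented as the primary result. The interim section adds weight to this: it lets the monitoring committee consider stopping when the primary outcome reaches p < 0.001, and the committee cannot apply that rule without knowing which p-value is meant.

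Second, whether the 50% control rate applies depends on whether leiomodin is inside the endpoint, and the document answers that in two ways.

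**Working it through.** **Inputs.** From the Sample size section: 50% v 30%, 80% power, 5% significance (sidedness not stated), 10% loss, 115 per arm, leiomodin about 60%. From the Randomisation section: 1:1 allocation.

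**Step 1. Reproduce the 230.** Two-sided 5%, pooled variance under the null, mean proportion 0.40:

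n0 = [1.96·√(2·0.4·0.6) + 0.842·√(0.5·0.5 + 0.3·0.7)]² / 0.2² = 93.0 per arm.

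Continuity correction: n = (n0/4)·[1 + √(1 + 4/(n0·0.2))]² = 102.8, so 103 per arm.

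Loss: 103/0.9 = 114.4, so 115 per arm and 230 in total. This matches exactly. Without the continuity correction the total is 208. The 230 is therefore one two-sided 5% test, with nothing set aside for a second.

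**Step 2. Count the comparisons.** Positivity and level, each for HNPs and for leiomodin: 2 × 2 = 4. Testing antibodies separately would add more.

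**Step 3. Any-one-counts rule, each test at 5%.** Family-wise error = 1 − 0.95^m for independent tests:

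- m = 2: 1 − 0.9025 = 9.8%
- m = 4: 1 − 0.8145 = 18.5%

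With an assumed correlation of 0.5 between the tests, simulation gives about 9.0% and 15.6%.

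**Step 4. Bonferroni applied to the primary tests (assumed).** Power for HNP positivity, 50% v 30%, by exact enumeration of the two binomials at 103 per arm:

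| Tests | Alpha | Chi-square | Continuity-corrected | Total N for 80% (method of Step 1) |
|---|---|---|---|---|
| 1 | 0.05 | 85% | 81% | 230 |
| 2 | 0.025 | 77% | 72% | 274 |
| 4 | 0.0125 | 68% | 62% | 318 |

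**Step 5. Leiomodin inside an any-positive endpoint.** The proportion positive for HNPs or leiomodin cannot be below the larger of the two rates: P(either) ≥ max(0.50, 0.60) = 0.60. This needs no independence assumption, only that both pilot rates describe the trial population. The upper limit is 100%, since 0.50 + 0.60 exceeds 1. Under independence it would be 1 − 0.5·0.4 = 80%. No value in this range is the 50% used for sizing.

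**Step 6. Titres.** Power for the level comparisons cannot be calculated, because the document gives neither a difference nor a standard deviation.

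**The case against.** The best counter-argument is that power need not fall. If any one success counts, HNP positivity was the harder of the two positivity contrasts. Assume leiomodin falls by the same 40% (60% to 36%): exact power for leiomodin alone is then 93% at 0.05 and still 85% at 0.0125 (about 81% continuity-corrected). The chance of at least one success therefore stays above 80% even after a four-way split. This stands. A reader might infer from Step 4 that the trial is underpowered, but the document supports only that its power is undefined.

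Four other stronger readings are tempting and should not be drawn.

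- **Eleven tests.** Up to 11 antibodies can be counted in the document, but the list overlaps (the VGKC complex includes LGI1 and CASPR2) and the cell-based assays depend on immuno-histology. The 50% is the rate for an HNP in general, not for any single antibody. Figures for 11 tests would misuse it.
- **A composite that hides the effect.** If HNPs and leiomodin were independent and only HNP positivity fell, an either-positive endpoint would have little power. That requires an effect sparing leiomodin, whereas the trial's mechanism covers cross-reacting antibodies including leiomodin. If both fall by 40% under independence (80% to 1 − 0.7·0.64 = 55%), power is 97%.
- **Levels listed twice.** The secondary item is "Mean change in serum levels or titres of antibodies to HNPs or leiomodin"; the primary refers to level at 24 months. These are related but different variables.
- **A promised correction of the primary tests.** The multiplicity phrase follows a sentence on cognitive tests and names no family, so applying it to the antibody tests is an inference.

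It can also be said that this is phase II and that the multiplicity method belongs in the analysis plan. The method does. Choosing the primary variable and matching the sample size to it is a protocol matter, and this document sets its own 80% power, 5% level and efficacy stopping rule.

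**Conclusion.** The point holds. The arithmetic of the 230 is sound, but it belongs to HNP positivity alone, while the stated primary outcome has at least four components and no rule for combining them. The consequence depends on the reading: a family-wise error of up to about 19% if four independent tests are run at 5% and any one counts, or power for the sized contrast of 77% (72%) or 68% (62%) if alpha is split two or four ways. These sizes rest on Bonferroni, on the number of tests and on 103 evaluable patients per arm; correlated tests would give a smaller error rate.

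The inconsistency over leiomodin is confined to one parenthesis in the Background. It still matters, because including leiomodin in an any-positive endpoint moves the control rate to at least about 60%.

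**What to change.** 1. Name the sized endpoint as the single primary variable: proportion positive for at least one antibody in a fixed HNP panel at 24 months, doxycycline v placebo, two-sided 5%.
2. State explicitly whether leiomodin and DJ-1 are in the panel, and use the same definition in the abstract, Background, outcome and analysis sections.
3. Move separate leiomodin positivity, individual antibodies and all levels or titres to secondary, and apply the multiplicity correction there.
4. Freeze the panel and the positivity cut-offs before the first unblinded interim look.
5. If leiomodin stays in the primary, restate the control rate (at least about 60% for an any-positive endpoint) and the power. If several primary tests are kept, state the success rule, the split alpha and the resulting power.

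Items 1 to 4 cost a short amendment of wording, with no extra patients or assays. The price is fewer ways to claim primary success. Keeping several primary tests under a Bonferroni split, with 80% power retained for the HNP contrast, would instead need about 274 patients for two tests or 318 for four.
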